### Secondary outcome

The secondary outcomes of the study will include growth and the treatment outcomes of children with SAM. In order to assess the growth performance of the children, weight, height/length and MUAC will be measured following the standard procedure based on the Ethiopian national protocol for the management of SAM [14].

To determine treatment outcome, the death rate, recovery/cure rate, defaulter rate, non-responder rate, the average rate of weight gain, and the mean length of stay of children in the SC will be calculated based on the Ethiopian guidelines for the management of acute malnutrition [11]. The proportion of cases that will have relapsed SAM within the 6 months follow up period will be calculated. Children will be considered to have a relapse, when their WFL/H is less than 70% of the WHO reference median or less than – 3 Z score and/or having bilateral pitting edema and/or MUAC < 11.5 cm.

Detail data on the socio-demographic situation of the family and other relevant data such as the mothers/ caregivers’ knowledge of childcare, dietary data, household food insecurity data, and data on mother/ caregiver-child relationship, the presence of family conflict, and the previous medical conditions will be collected using a structured questionnaire. The health workers will administer the Amharic version of the questionnaire to the mothers/ caregivers through a face-to-face interview during the transition phase of the inpatient management of SAM when the clinical condition of the child is improved and the mothers/ caregivers become more relaxed. To collect follow up data, a separate structured questionnaire will be used during home visits. Data on the adherence of mothers/ caregivers under the intervention group towards the implementation of the simulation activities, the reason for non-adherence if any, the support and involvement of other family members in the stimulation interventions will also be gathered in the follow-up visits (Additional file 1 & Additional file 2).

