### Personnel for the study

Health workers who will be recruited from the SC of each of the health facilities will take the responsibility for the recruitment; follow up of children during the SC admission period, for supporting the intervention workers/play guides and for the collection of enrollment and other data. Depending on the caseload in the SC of the health facility, one or two health workers will be included in the study team from each of the health facilities.

For each of the health facilities, one young female intervention worker/ play guide who have completed at least grade 10 will be recruited from the local community considering their child-friendliness. In the intervention health facilities, the intervention workers/ play guides will assume the responsibility of facilitating the stimulation intervention during the inpatient care and for the period of 6 months after discharge through a home visit. They will also provide health education, conduct home-based follow up, collect follow up data, participate in the preparation of suitable toys from locally available materials, help mothers/ caregivers and other family members, and equip them with the essential skills for the implementation of the intervention. For each of the control health facilities, the intervention worker will only be responsible for providing health education, conducting home-based follow-up, and collection follow-up data. A separate mobile team of testers/ outcome assessors will be recruited considering their academic background and previous experience to collect anthropometric data and administer developmental tests. They will be unaware (Blind) to the allocation status of the children and the health facilities to avoid measurement bias.

Experienced supervisors will be recruited to oversee the activities of the health workers, the team of testers/ outcome assessors and the intervention workers. The field-level project coordinator under the direct guidance of the principal investigator will be responsible for the overall coordination and follow up.

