### Training of the study team

Intensive training will be given for the study personnel by a team of senior trainers. Separate training will be provided for each of the study teams considering the allocation status of their health facilities, their role in the study and their professional experience. For the intervention health facilities, health workers will be trained on the basis of psychosocial stimulation and the study procedures including recruitment and data collection procedures, facilitation of psychosocial stimulation, and facility-level follow up procedures. The training of the intervention workers/play guides will focus on the basics of childcare, child growth, and development, about the communication methods and other intervention-related issues such as the study procedures, the facilitation of the stimulation intervention and follow up procedures. For the control health facilities, the training of both the health workers and intervention workers/ play guides will not include the stimulation intervention related topics. The measurement team will also be trained on the standards of anthropometric measurement and administration of development tests. In all the training sessions, the trainees will go out to the field to practice the practical components of the training.

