### Outcome measurement and tools

All outcomes will be assessed four times throughout the follow-up period. These include before the intervention when the child will be transferred from Phase I to the Transition Phase (baseline measurement), upon discharge from the SC of the health facilities and at 3 and 6 months where all mothers/ caregivers will be asked to bring their child to the health facilities for the latter two measurements. As per recommendations of the pilot study conducted to assess the feasibility and reliability of the sequence of various measurements, measurements requiring greater concentration (developmental tests) will be administered first that will be followed by the anthropometric measurements which will require less concentration [17].

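### Recovery and non-response are not tied to the blinded team's discharge measurements and, by inference, rest on facility staff who know the arm

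*Protocol article*

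**What the plan says.** All references are to the protocol article.

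- **Secondary outcome.** The treatment outcomes are "the death rate, recovery/cure rate, defaulter rate, non-responder rate, the average rate of weight gain, and the mean length of stay of children", and they "will be calculated based on the Ethiopian guidelines for the management of acute malnutrition". No assessor and no data source is named. Relapse is given explicit anthropometric and oedema thresholds in the same section; recovery and non-response are left to the guideline.
- **Personnel for the study.** SC health workers are responsible for recruitment and for "follow up of children during the SC admission period, for supporting the intervention workers/play guides and for the collection of enrollment and other data". Separately, "A separate mobile team of testers/ outcome assessors will be recruited considering their academic background and previous experience to collect anthropometric data" and to administer the developmental tests. Of this team the section says: "They will be unaware (Blind) to the allocation status of the children and the health facilities to avoid measurement bias".
- **Training of the study team.** In intervention facilities "health workers will be trained on the basis of psychosocial stimulation and the study procedures including recruitment and data collection procedures", and also in facilitating stimulation. In control facilities the stimulation topics are left out.
- **Outcome measurement and tools.** All outcomes are assessed four times: at transfer from Phase I to the Transition Phase, and then "upon discharge from the SC of the health facilities and at 3 and 6 months".

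**The concern.** Blinding is stated for the people who take anthropometry and give the developmental tests. It is not stated for whoever decides that a child has recovered or has not responded. Those categories arise at the end of inpatient care, and the article places inpatient follow-up with SC staff. In intervention facilities these staff have been taught the intervention and support its delivery.

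A worker who expects stimulation to help could, without intending it, class a borderline child as recovered rather than non-responder, or judge the child ready to leave sooner. If this happens more in one arm, it cannot be told apart from a treatment effect. Treatment outcome appears in the title and the hypothesis, and the Discussion presents it as an under-researched area where the trial will add evidence, so these results will be read closely even though they are secondary.

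**Working it through.** **1. Who does what.**

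| Element | Assigned to | Knows the arm? | Stated or inferred |
|---|---|---|---|
| Inpatient follow-up; enrolment and other data | SC health workers | Yes (arm-specific training; support of play guides) | Duties stated; knowledge of the arm follows directly |
| Weight, length/height, MUAC; developmental tests | Mobile assessor team | No | Stated |
| Measurement at baseline and at discharge | Scheduled for all outcomes; anthropometry is the mobile team's task | No | Follows from two sections read together |
| Classing a child as recovered or non-responder | Not assigned | – | SC staff, by inference |
| Discharge date | Not assigned | – | SC staff, by inference |
| Weights used for the rate of weight gain | Not assigned | – | Blinded weights are available |

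Exposure therefore differs by outcome. Recovery and non-response depend on a classification that appears to be made by unblinded staff. Length of stay depends on the discharge date alone. For weight gain the numerator can be blinded, but the time denominator uses the same date. Development does not depend on staff classification, because blinded testers are named for the developmental tests.

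**2. Illustration for recovery.** The plan gives no figure for a coding shift, so this shows only how sensitive the comparison would be.

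Inputs from the article (Sample size determination): 72 children per arm, 8 per facility, ICC 0.05. Assumed: true recovery *p* of 70% or 80% in both arms, and a coding shift *b* in the intervention arm only.

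- Design effect = 1 + (8 − 1) × 0.05 = 1.35. Effective *n* per arm = 72/1.35 = 53.3.
- SE = √{[*p*(1 − *p*) + (*p* + *b*)(1 − *p* − *b*)]/53.3}.
- Probability of *P* < 0.05 = Φ(*b*/SE − 1.96) + Φ(−*b*/SE − 1.96).

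| *p* | *b* | SE | *b*/SE | False-positive rate |
|---|---|---|---|---|
| 0.70 | 0.05 | 0.0863 | 0.58 | 8.9% |
| 0.70 | 0.10 | 0.0833 | 1.20 | 22.5% |
| 0.80 | 0.05 | 0.0734 | 0.68 | 10.5% |
| 0.80 | 0.10 | 0.0685 | 1.46 | 30.9% |

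If the variance at *p* = 0.80 is used for both arms, SE = √(2 × 0.80 × 0.20/53.3) = 0.0775, and the last two rows become 9.9% and 25.2%. With a t reference on 18 − 2 = 16 degrees of freedom, that 25.2% becomes 22.9%.

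**3. Illustration for length of stay.** Assumed SD 5 to 8 days (not in the article). SE = SD × √(2 × 1.35/72), which is 0.97 days at SD 5 and 1.55 days at SD 8. A 1-day shift in discharge practice in one arm gives 18% (SD 5) to 10% (SD 8) false positives; a 2-day shift gives 54% to 25%. On 16 degrees of freedom the 54% becomes 49%.

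**The case against.** The strongest reply is that a reader might infer more than the article says. Three stronger readings are tempting, and the text does not support them.

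- **That the treatment outcomes come from facility staff.** No section says so. The link rests on the health workers' inpatient follow-up and on an unspecified category of other data. No section assigns discharge decisions or outcome coding to anyone. The inference is natural, but it remains an inference.
- **That the blinded team's measurements are not used for these outcomes.** No section says this either. Weight is anthropometry, which is that team's task, and all outcomes are scheduled at baseline and discharge. Blinded weights are plainly available for weight gain, so that outcome is not exposed in the same way.
- **That every child has a blinded discharge measurement.** Children who die or default in the SC may have none.

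It can also be said that a condensed article leaves data sources to fuller documents; that staff cannot be blind to a play programme in their own facility; that the guideline's exit criteria are not reproduced, so one discharge visit may not suffice to apply them; and that all the bias figures are assumed.

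Most of this stands, and it limits the point to recovery and non-response, with a caveat for the discharge date. It does not remove the point. The article does fix who is blinded and for which tasks, and that remit does not include classifying recovery or non-response. That staff cannot be blinded is a reason to base the classification on the measurements of people who can be.

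**Conclusion.** The concern holds in a limited form. Recovery and non-response are derived from the guideline without being tied to blinded measurements, while the stated division of work leaves inpatient follow-up with staff who know the arm. Detection bias in these secondary outcomes is a fair inference, not a documented fact.

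Its size cannot be derived from the article. The illustrations show that a 5-point shift in coding would roughly double the 5% error rate and that a 10-point shift would raise it to between 20% and 31%, depending on assumed recovery and on the variance used. They say nothing about whether such shifts are likely. The larger length-of-stay figures concern an outcome that the fix below does not repair.

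No number in the plan is wrong on this point. This is a cheap improvement to secondary outcomes and does not threaten the trial's main comparison.

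**What to change.** In the Secondary outcome section, state the following:

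1. For children with a discharge measurement, recovery and non-response are classified centrally by someone blind to facility. That person applies the guideline's existing criteria, as far as they can be applied, to the blinded team's discharge weight, length/height and MUAC plus a recorded oedema field. Any criterion that cannot be judged from that visit should be named.
2. Facility exit codes are reported beside the blinded classification, by arm, so that disagreement can be seen.
3. The rate of weight gain uses the blinded team's baseline and discharge weights.
4. Death and default remain facility-recorded.
5. Length of stay and the time denominator of weight gain are reported with the caveat that the discharge date appears to be set by unblinded staff.

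The cost is one derivation rule and one extra field at a visit already scheduled. No clinical rule changes, and recruitment had not begun when the article was submitted. Two limits remain: children who die or default have no blinded classification, and the timing of the discharge measurement still follows the facility's decision.

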### Data management and analysis

Two independent data entry operators will check, code, and enter the collected data into Epi Info Version 7 Statistical Software. STATA Version 15 Statistical Software will be used for the statistical analyses. The anthropometric Z-scores and percentile of the median will be calculated using the WHO Anthro Version 3.2.2 Statistical Software. Proportions, percentages, measures of central tendency together with measures of dispersion will be used to summarize the collected data. For each test item in the developmental measures, a binary outcome variable with the categorical score of a pass or fail will be created where; pass will be considered for items that the child will be tested and passed while fail will be considered for items that the child will be tested and failed or refused. No opportunity to perform will be considered for items that the child will not be tested for due to various reasons including medical conditions, which will be treated as missing values. A numerical score will be computed by adding up the points of all items for each of the developmental dimensions. For the social-emotional dimensions of the child development that will be measured using ASQ: SE, a numerical score will be computed by adding up the points of all items on the questionnaire. From the anthropometric data of weight, height, and MUAC, the nutritional status of children will be determined. The proportion of cases in either group of the study that will be recovered, defaulted, and dead or relapsed within the study period will be also calculated and reported.

In a cluster RCT, participants within the same cluster may be more similar than those in different clusters, which may lead to the correlation of observations within the clusters. Failure to account this in the analysis and the subsequent use of standard statistical methods will make the resulting standard error of the intervention effect too small, along with the confidence interval and *P*-value [22]. In all the analyses that will be conducted using the data of all randomized study subjects, the clustering nature of the data will be considered. In order to assess the overall effect of the intervention by controlling other potential contributing factors, a Generalized Linear Mixed Model (GLMM) that is flexible to address the outcome variables to be measured in this study will be used.

The model is appropriate for the present study considering the correlated nature of the repeated measurements from each study subject and from the hierarchical structure of data that study subjects nested in health facilities (clusters). In all the analysis variables with a *p*-value < 0.05 will be considered statistically significant.

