## Background of the study

Globally approximately 151 million (22%) children under 5 years of age suffer from stunting and nearly 51 million (7.5%) were wasted in 2017. More than one-third of all stunted and more than one-quarter of all wasted children under 5 years of age are living in Africa [1]. According to the Ethiopian Demographic and Health Survey (EDHS) report, the prevalence of stunting, wasting and underweight among children under 5 years of age was 38, 10 and 24% respectively [2].

In view of the fact that malnutrition remains a direct or indirect cause of child mortality, the WHO developed the standard protocol to improve its management process and the survival of children. Considering the benefits of early child development programs in improving the long term developmental potential of children suffering from undernutrition, the protocols suggested the inclusion of emotional and physical stimulation through play programs during rehabilitation and after discharge [3]. However, few studies were conducted globally to examine the effect of the stimulation interventions provided in conjunction with the routine medico-nutritional care of children with SAM admitted in the nutrition rehabilitation unit. The study conducted in Bangladesh found out that the inclusion of the psychosocial stimulation interventions with the routine medico-nutritional care improved the mental development, motor development, weight-for-age Z-score and no change was noted for children behavior [4]. In Jamaica, the stimulation program showed a significant impact on the mental development of severely malnourished children [5]. In Ethiopia, the only study conducted among children with SAM admitted in the Stabilization Center (SC) of Jimma University Hospital revealed that the intervention significantly improved the gross motor functions during their hospital stay and fine motor functions with only small effect size after discharge from the hospital. However, it did not contribute significantly to linear growth and nutritional outcomes [6].

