## Hypothesis and objectives of the study

### Hypothesis

It is hypothesized that children with SAM age 6–59 months admitted in the SC who receive psychosocial stimulation interventions with the routine inpatient care and for 6 months after discharge will have a significantly greater improvement on their development, growth and treatment outcomes compared to those who receive the routine care alone.

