### Sample size determination and sampling technique

The sample size for the study is determined by considering the longitudinal (repeated measure from each subject over time) and clustered (study subjects nested in health facilities (clusters)) nature of the study. First, the sample size is determined by considering the longitudinal nature of the study using the formula for comparing two means [12] with the aim of detecting a 10% improvement from the mean + SD value of 15.8 + 4.4 for fine motor score of developmental domain which was obtained from similar study conducted in Ethiopia [6]. Four measurements are planned in the study. These include before the intervention when the child will be transferred from Phase I to the Transition Phase (baseline measurement), upon discharge from the SC of the health facilities and at three and 6 months. Thus, the number of time points of measurement taken from each study subjects; t = 4, type one error = 0.05, power = 90%, smallest meaningful difference d = 10% and the assumed correlation (r) of the repeated measures *r* = 0.02. Consequently, a sample of 44 children with the diagnosis of SAM satisfying the admission criteria to the SC per group will be required under individual randomization. The calculated sample size under individual randomization was further adjusted to account for the effect of clustering with an assumed Intracluster Correlation Coefficient (ICC) ρ = 0.05. Since this study is a trial with a fixed number of equal-sized clusters (k) the required sample size per group is obtained using the formula proposed by Hemming [13]. After considering, 20% of the calculated sample size for the potential dropout, 68 children will be required for each of the study groups. The corresponding number of individuals in each of the health facilities (clusters) is determined using the formula [13]. Accordingly, approximately eight study subjects from each of the study health facilities (clusters) will be required making the final sample 72 children with SAM for each of the study groups. Thus, 144 children with SAM age 6–59 months satisfying the inpatient admission criteria will be recruited and included in the two study groups. Based on the recommendation of Hemming [13] this trial is feasible since the number of clusters k = 9 per group is greater than the product of the number of individuals required under individual randomization (*n* = 44) and ICC (ρ = 0.05). Based on the report of the Silti Zone Health Office, the achievement of the target sample of children with SAM is feasible during the recruitment period.

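### The hypothesis concerns improvement, but the plan points to an overall effect averaged over four visits, one of them before the intervention, and gives baseline no role

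*Protocol article*

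**What the plan says.** The protocol article describes the deciding comparison in several places.

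- **Hypothesis:** children who receive stimulation "will have a significantly greater improvement on their development, growth and treatment outcomes" compared with routine care. This is a statement about change.
- **Primary outcome:** child development, with no time point and no change measure.
- **Outcome measurement and tools:** "All outcomes will be assessed four times throughout the follow-up period". The first assessment is "before the intervention when the child will be transferred from Phase I to the Transition Phase (baseline measurement"; the others are "upon discharge from the SC of the health facilities and at 3 and 6 months". No visit is ranked above another.
- **Sample size determination and sampling technique:** "the number of time points of measurement taken from each study subjects; t = 4". The four are listed there too, and baseline is one of them.
- **Data management and analysis:** a generalized linear mixed model will be used "In order to assess the overall effect of the intervention by controlling other potential contributing factors". It is justified by the repeated and clustered data. The section names no visit, no arm-by-time term and no use of the baseline score. Its significance rule is that a p-"value < 0.05 will be considered statistically significant".

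**The concern.** A test of improvement compares the arms on change from baseline, or on post-baseline scores adjusted for baseline. An arm effect averaged over every measured visit is a different quantity. Randomization makes the expected arm difference zero at the pre-intervention visit, so including that visit with full weight pulls the average toward zero. The analysis section does not say that this is what will be fitted. However, the sample size treats baseline as one of four visits that all show the full difference, and the analysis wording fits the same reading.

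Two things are at stake. The estimate could understate the benefit that the hypothesis describes, and the stated 90% power would not apply to it.

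**Working it through.** **Inputs from the sample size section.** Fine motor mean 15.8 and SD 4.4; difference 10% of 15.8 = 1.58; t = 4; correlation of repeated measures r = 0.02; type I error 0.05; power 90%; ICC 0.05; 9 clusters per group; dropout 20%. Sidedness is not stated. Two-sided is assumed because it reproduces the plan's figure; one-sided gives 36.

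**1. Reproduce the plan's figure.** For a mean over t visits, n per group = 2(1.960 + 1.282)² × SD² × V / d², with V = [1 + (t − 1)r]/t.

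- Four visits: V = 1.06/4 = 0.265, so n = 406.85 × 0.265 / 2.4964 = 43.19, or 44. This is the stated figure.
- Three post-baseline visits: V = 1.04/3 = 0.3467, so n = 56.5, or 57.
- One visit: V = 1, so n = 163.
- Clustering: 44 × 0.95 / (9 − 44 × 0.05) = 41.8/6.8 = 6.15 per cluster, or 55.3 per group, rounded to 56. Then 56 × 1.2 = 67.2, or 68, and 68/9 = 7.6, or 8 per cluster, giving 72 per group. All stated figures reproduce.

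At these inputs, 44 arises as a four-visit mean in which baseline also carries the full 1.58 points.

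**2. Put the expected baseline difference at zero.** (0 + 1.58 + 1.58 + 1.58)/4 = 1.185, which is 0.75 of 1.58. The required n becomes 43.19/0.75² = 76.8, or 77.

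**3. Power at 44 per group, before clustering.** Power = Φ(difference/SE − 1.960), with SE = 4.4 × √(2V/44).

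- Four-visit mean as sized: SE 0.483; 1.58/0.483 = 3.27; power 90.5%.
- Four-visit mean, zero at baseline: 1.185/0.483 = 2.45; power 68.9%.
- Mean of three post-baseline visits: SE 0.552; 1.58/0.552 = 2.86; power 81.6%.

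**4. Other correlations (assumed range).** Adjusting the post-baseline mean for the baseline score gives V = (1 + 2r)/3 − r². Power at 44 per group, before clustering:

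| r | Four-visit mean, zero at baseline | Post-baseline mean | Post-baseline mean, baseline-adjusted |
|---|---|---|---|
| 0.02 | 69% | 82% | 82% |
| 0.2 | 52% | 69% | 73% |
| 0.5 | 36% | 54% | 74% |
| 0.8 | 28% | 44% | 94% |

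**5. With clustering and dropout, r = 0.5 (assumed).** 72 less 20% is about 58 per arm. The design effect is 1 + (58/9 − 1) × 0.05 = 1.27. Approximate power is 37% for the four-visit mean with zero at baseline, 56% for the post-baseline mean, and 76% for that mean adjusted for baseline.

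These calculations use a normal approximation, equal correlation between visits and a constant post-baseline effect. The last step also applies the same design effect to every contrast.

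**The case against.** The strongest reply is that the analysis section never says the arm effect is a main effect over four visits. A mixed model can take baseline as a covariate or carry an arm-by-time term, and an article may leave that specification to a fuller document. This stands as far as the model goes, so the dilution is conditional on how the model is fitted. It does not remove the mismatch in the text. The hypothesis is about change, the named target is an overall effect, and the one place that shows the intended contrast counts the pre-intervention visit in it.

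A reader might go further and infer that the error rate per domain exceeds 5% because any of three post-baseline visits could carry the claim. The document does not support that. It plans no visit-by-visit tests and does not say that significance at one visit suffices. If only the overall effect is tested, the error stays at 5% per domain. It would be about 10–14% (correlation 0.8 down to 0.02) only under an any-visit rule.

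A reader might also conclude that month 6 should decide the trial. Nothing in the document ranks it first, and the choice costs power: 39% at 44 per group with r = 0.02, or about 51% baseline-adjusted with 58 per arm, r = 0.5 and clustering. The Background report on the earlier Ethiopian trial, that stimulation "significantly improved the gross motor functions during their hospital stay and fine motor functions with only small effect size after discharge from the hospital", does not settle the matter either. It contrasts two different domains, not two time points within one.

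**Conclusion.** The point holds in a limited form. The hypothesis and the stated analysis target do not match, baseline has no stated role, and the sample size rests on a four-visit mean that includes a visit before the intervention. If the overall effect is fitted that way, it estimates 1.185 instead of 1.58 points. Power at the stated 44 per group is then about 69% instead of 90%, before clustering and at the protocol's r = 0.02. The loss is larger at higher correlations.

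This rests on a two-sided test, a constant effect at the three post-baseline visits and a zero expected difference at baseline. It also rests on reading the overall effect as the contrast used for sizing, which the text suggests but does not state.

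**What to change.** In Data management and analysis, define the overall effect as the mean of the arm differences at discharge, 3 months and 6 months. Estimate it from the mixed model with categorical time, arm-by-time terms and the baseline score as a covariate (or with arm means constrained equal at baseline). Report the differences at single visits as secondary, which also rules out an any-visit claim.

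In the sample size section, restate the power for this contrast: about 82% at 44 per group with r = 0.02, before clustering.

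**Cost.** A few sentences and a revised power statement. The baseline score is already collected and no new measurements are needed. The contrast can be fixed before any outcome data are seen, since recruitment had not started when the article was submitted. More children would be needed only if the sponsor wants 90% power on the stated inputs. The protocol's own steps then give 57 × 0.95 / (9 − 2.85) = 8.80 per cluster, or 79.2 per group, rounded to 80. Next, 80 × 1.2 = 96, and 96/9 = 10.7, so 11 per cluster and 99 per group in place of 72. Otherwise the current size can stand with the lower power stated.
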